## Abstract

**Introduction:**

A subgroup of adolescent and young adult childhood cancer survivors (AYACCS) are at increased risk of psychological distress. Despite this, AYACCS experience difficulties accessing psychological support. E-mental health (e-MH) may offer a solution to reduce this treatment gap. However, research examining e-MH for AYACCS has experienced difficulties with recruitment, retention and adherence. Such difficulties may relate to: (1) help-seeking behaviour and/or (2) e-MH acceptability. The overall study aims are to: (1) examine potential associations between health service use factors, informed by Andersen’s behavioural model of health services use, and help-seeking behaviour; (2) examine attitudes towards e-MH interventions; and (3) explore perceived need for mental health support; past experience of receiving mental health support; preferences for support; and barriers and facilitators to help-seeking.

**Methods and analysis:**

An online and paper-based cross-sectional self-report survey (98 items) and embedded qualitative interview study across Sweden, with a target sample size of n=365. Participants are aged 16–39 years, diagnosed with cancer when 0–18 years and have completed successful cancer treatment. The survey examines sociodemographic and clinical characteristics, actual help-seeking behaviour, attitudes towards e-MH, stigma of mental illness, mental health literacy, social support and current symptoms of depression, anxiety, and stress. Survey respondents with past and/or current experience of mental health difficulties are invited into the qualitative interview study to explore: (1) perceived need for mental health support; (2) past experience of receiving mental health support; (3) preferences for support; and (4) barriers and facilitators to help-seeking. Potential associations between health service use factors and help-seeking behaviour are examined using univariable and multivariable logistic regressions. Qualitative interviews are analysed using content analysis.

**Ethics and dissemination:**

Ethical approval has been obtained from the Swedish Ethical Review Authority (Dnr: 2020-06271). Results will be disseminated in scientific publications and academic conference presentations.

**Trial registration number:**

ISRCTN70570236.

Strengths and limitations of this studyThe mixed methods design may aid a rich and insightful understanding of the investigated phenomena.Results may be used to inform the development of acceptable, relevant, and accessible mental health interventions for adolescent and young adult childhood cancer survivors.Reasons for not receiving a mental health intervention are not explored and only those who report receiving support in the past 6 months are defined as help-seeking.This approach may exclude adolescent and young adult childhood cancer survivors who have attempted to seek formal help (help-seeking) but did not receive help.No conclusions concerning cause and effect can be drawn given the cross-sectional design.

## Introduction

Medical improvements have resulted in an overall 5-year survival rate of 81.2% from cancer diagnosed during childhood (0–18 years) in Northern Europe.^1^ However, significant challenges, such as late effects, remain after treatment completion.^2 3^ Survivors of childhood cancer report a number of long-term adverse physical and developmental outcomes^4–6^ and social and economic impacts, including poorer educational and occupational achievements.^7 8^ A further common late effect is symptoms of psychological distress, for example, post-traumatic stress, anxiety and depression, symptoms of which have been found to persist decades postdiagnosis.^9–11^ Difficulties with psychological distress are further complicated given that adolescence is a period of increased vulnerability to mental health problems,^12^ with difficulties such as depression and anxiety commonly first appearing before 24 years of age.^13^ Indeed, individuals diagnosed with cancer during childhood, adolescence and young adulthood have been found to be at an increased likelihood of being prescribed hypnotics and anxiolytics^14 15^ of using antidepressant medication over the long-term,^16^ and are at an elevated risk of suicide.^17^ As such, adolescent and young adult childhood cancer survivors (AYACCS), commonly defined as cancer survivors diagnosed during childhood currently aged between 15 and 39 years,^18^ are particularly vulnerable to experiencing adverse psychological and social outcomes, and there is a significant need for long-term care and support.^5^ However, despite a clear need for the provision of mental health support, a mental health treatment gap remains, with few AYACCS being offered professional psychological support.^19–22^ Reasons for this treatment gap may pertain to a lack of qualified healthcare professionals, poor service provision, geographical barriers^23^ and public stigma (eg, the general public holding negative beliefs about cancer survivors, eg, being less competent).^24^

E-mental health (e-MH), defined as the provision of psychological support via information technology and new media (eg, online, smartphone applications, video conferencing),^25^ may represent a solution to reduce the mental health treatment gap.^26^ One example of e-MH is internet-administered cognitive behavioural therapy (ICBT). ICBT has been found to be effective for a range of common mental health difficulties, such as depression and anxiety,^27^ including for young adult populations^28^ and has been found to be as effective as traditional face-to-face CBT.^29^ e-MH interventions may help overcome practical barriers associated with accessing traditional face-to-face psychological support (eg, geographical, financial and time-related barriers)^30^ that have been observed within the AYACCS population.^31^ Furthermore, e-MH is associated with anonymity and privacy^32^ thus potentially overcoming barriers associated with public stigma. Indeed, research has identified that the provision of e-MH interventions may be a potential solution for the AYACCS population.^33–38^ However, research examining e-MH support for an AYACCS population has encountered challenges with recruitment, attrition, and internet use.^34 38^ For example, one study examining the feasibility and acceptability of e-MH recruited only 28 participants over a 12-month period and experienced almost 30% attrition.^38^ Another feasibility study of e-MH for adolescents and young adults who had experienced cancer during the adolescent period recruited only 6 participants from a total of 320 potential participants invited into the study, and experienced a 100% attrition rate.^34^ Indeed, a recent review of e-Health interventions for AYACCS concluded that engaging the population was challenging, and there is currently a lack of literature concerning how to better engage the population.^36^ However, challenges with recruitment, attrition and internet use are common in the field of e-MH research.^39–41^ Potentially, challenges with recruitment, attrition and internet use may be related to help-seeking behaviour and the acceptability of e-MH for the population.

### Help-seeking behaviour

Low rates of formal help-seeking behaviour for mental health difficulties is common among an adolescent and young adult population in general.^42^ A number of potential barriers to help-seeking have been identified, including stigma, embarrassment, and poor mental health literacy (MHL).^43 44^ AYACCS report difficulties with stigma and alienation in relation to the cancer disease^45^ and as such may be reluctant to identify themselves as experiencing mental health difficulties. Furthermore, while social support has been found to facilitate help-seeking behaviour for mental health difficulties in adolescent and young adult populations,^43^ AYACCS commonly report difficulties with social withdrawal and loneliness.^46 47^ However, at present there is a lack of research concerning help-seeking behaviour for mental health difficulties experienced by an AYACCS population.

A frequently used approach for identifying factors associated with help-seeking is Andersen’s behavioural model of health services use behaviour.^48^ The model hypothesises a number of factors to be associated with help-seeking behaviour: (1) predisposing factors including sociodemographic variables (eg, age and gender), and health-related beliefs and knowledge^49^; (2) enabling factors relating to logistical elements to receiving care and resources (eg, financial factors and social support)^50^; (3) external environmental factors (eg, location); and (4) need-related factors (eg, symptoms of psychological distress). Recently, the model has been adopted to examine factors associated with accessing both traditional and e-MH services within a young adult (aged 18–39 years) population.^32^ Interestingly, the study identified a weaker utilisation of e-MH by young people who had experienced negative childhood experiences during childhood (eg, family conflict, bullying or lack of affection).^32^ This finding is of particular importance seeing that negative experiences of childhood are normally associated with increased mental healthcare utilisation.^51^ Furthermore, given evidence to suggest some AYACCS may experience bullying related to their cancer experience^52^ and poor family functioning for example conflict,^53^ it may be important to examine whether negative childhood experiences are associated with reduced mental healthcare utilisation in an AYACCS population. Furthermore, to the best of our knowledge, Andersen’s behavioural model of health services use has not yet been applied to an AYACCS population and factors associated with help-seeking in the population remain unclear.

### Acceptability

While adolescents appear to consider e-MH interventions to be potentially acceptable, they still report a preference for face-to-face over e-MH interventions.^54^ Indeed, there is some indication e-MH resources are not widely accessed by young people.^55^ One potential difficulty may be related to what has been coined the ‘*technology push’*, whereby e-MH solutions are designed to fit available technology, rather than to meet the unmet needs and preferences of end-users.^56^ Furthermore, research indicates poor uptake and ongoing use of e-MH interventions that have been implemented into healthcare settings within the general population.^57^ As such, there is a need to understand preferences and attitudes towards e-MH interventions within specific populations, via both quantitative and qualitative research, to inform future e-MH developments.^58^ To the best of our knowledge, there has been no exploration to date of the attitudes and preferences towards e-MH interventions within an AYACCS population. In addition, tailoring e-MH interventions to specific patient groups has been associated with increased effectiveness^59^ and adherence.^60^ Rates of attrition may be reduced, and adherence increased, if the perspective of the population using the intervention is taken into account when developing e-MH interventions.^61^ Furthermore, research into the psychological needs of an AYACCS population indicates a need for increased focus on the specific psychological and psychosocial needs of the population to enable to provision of more tailored support to the cancer experience.^62^ As such, there is need to explore AYACCS general preferences for psychological support, including potential intervention content.

### Study aims and research questions

The overall aims of the study are to: (1) examine potential associations between health service use factors, informed by Andersen’s behavioural model of health services use, and help-seeking behaviour; (2) examine attitudes towards e-MH interventions; and (3) explore perceived need and past experiences of mental health support, preferences for support, and barriers and facilitators to help-seeking. Specifically, the following research questions will be examined:

Are there associations between predisposing, enabling, environmental, and needs-related health service use factors, informed by Andersen’s behavioural model of health, and help-seeking behaviour within an AYACCS population?What attitudes are held by an AYACCS population towards e-MH interventions?What is the perceived need for mental health support within an AYACCS population?What are AYACCS experiences of past receipt of cancer-specific and non-cancer-specific mental health support?What preferences do an AYACCS population hold towards mental health support related to their cancer experience?What are the barriers and facilitators do an AYACCS population experience seeking help for mental health support related to their cancer experience?

## Method and analysis

### Study design

An online and paper-based, cross-sectional, self-report survey and embedded qualitative interview study across Sweden. The study has been registered in the ISRCTN clinical trial registry (ISRCTN70570236).

### Eligibility criteria

Eligible participants will: (1) be an adolescent or young adult, aged 16–39 years, at study start; (2) have been diagnosed with childhood cancer when 0–18 years; (3) have completed successful cancer treatment (including relapses) at a minimum 3 months ago according to self-report; (4) be able to read and write in Swedish; and (5) currently reside in Sweden.

### Recruitment

A multifaceted approach to recruitment will be adopted, using two main strategies.

#### Swedish Childhood Cancer Registry

Personal identification numbers of AYACCS will be obtained from the Swedish Childhood Cancer Registry (National Quality Registry, initiated in 1982). Next, addresses will be obtained via NAVET, a population registry held by the Swedish Tax Agency. NAVET is continuously updated with important information about the Swedish population, including deaths and can, as such, provide current addresses and information concerning the vital status of AYACCS. The Swedish Tax Agency will provide this information via a secure online file transfer system (e-transport) on the same day information is requested by the study team. Study invitation letters will be sent to AYACCS on the same day that information is provided via e-transport in order to minimise the likelihood of inviting a deceased AYACCS. AYACCS will be invited to participate by the study team on a weekly basis, using blocks of 100 until the target sample size has been reached. Blocks will be selected randomly, with minimisation used to ensure balance between factors that may affect outcomes: sex (male; female); current age (16–24 years; 25–39 years); and age at diagnosis (0–12 years; 13–18 years).

Study invitation packs sent to home addresses will include a study invitation letter, study information, a link to the online survey via the U-CARE portal (www.u-care.se), a secure internet research platform to support data collection and provision of e-MH interventions,^63^ and a study log-in code. All potential participants identified via the Swedish Childhood Cancer Registry and invited via mail-out will be provided with a link to the online survey on the U-CARE portal and a study log-in code. In addition, given evidence to suggest the provision of choice between web-based and paper-based surveys can increase survey response rates among childhood cancer survivors,^64^ we will include a paper-based survey and freepost envelope with each invitation letter.

#### Technology-based approaches

Considering that response rates to mail-out surveys have declined over the past two decades,^65^ we will also use technology-based recruitment approaches shown to be effective.^66^ Indeed, social media recruitment is successful in recruiting young adult cancer survivor (aged 20–35 years) populations.^67^ Specifically, we will identify community-based organisations and support groups with an online presence for AYACCS in Sweden. Examples may include: the Swedish Cancer Foundation and Childhood Cancer Foundation and Young Cancer. Organisations and support groups will be asked to place advertisements on their websites; distribute advertisements via e-mail lists and e-newsletters; and post advertisements on social networking sites (eg, Facebook, Twitter, and Instagram).

Each online advertisement will include brief study information, a link to the online survey on the U-CARE-portal, and a study log-in code unique to each organisation and technologically based recruitment type to allow for the examination of success of each technology-based recruitment strategy. Organisations and support groups using social media will be encouraged to re-post the advertisement at regular intervals following evidence suggesting that re-posting is required to meet recruitment targets.^68^

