#### Sample size estimation

The Swedish Childhood Cancer Registry has some 9880 Swedish persons diagnosed when 0–18 years registered since 1982. However, some will have been classified as having a benign tumour, some have been registered twice and some will be deceased. As such, the number of potentially eligible cases will be lower and estimated to be approximately 5745. Sample size calculation indicated that a minimum of 365 participants would be required, with a power of 0.9 and p<0.05 (two-tailed). Assuming a response rate of approximately 40%, as indicated by a systematic review of participation rates in self-administered questionnaire studies with childhood cancer survivors,^69^ we estimate inviting 913 potential participants to achieve the required sample size.

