#### Actual help-seeking behaviour

The following items will be used to examine actual help-seeking behaviour: (1) emotional health difficulties related to the childhood cancer experience; (2) the type of support received by those who accessed support in the past 6 months and/or in the past (not including the past 6 months): (a) face-to-face individual or group support from mental health professional; (b) face-to-face support from a general practitioner/family doctor; (c) technology-administered mental health support (eg, online therapy programme, smartphone application, video conferencing or teleconferencing); (d) technology-administered support from a general practitioner/family doctor (eg, online, video conferencing or teleconferencing); (e) social media support group; (f) phone help-line; (g) family, partner or friend/s; (h) religious leader; and (i) other. Type of support will be categorised into: (1) face-to-face professional support; (2) technology-administered professional support; and (3) informal support (social media support group, family, partner, friends and religious leader). Those who sought support for mental health difficulties in the past 6 months and received support from a health professional either face-to-face or technology assisted will be defined as ‘help-seeking’.^70^

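### Random registry invitees and self-selected online volunteers feed one analysis with no term, stratum or sensitivity analysis for recruitment source

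*Protocol article*

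**What the plan says.** The Recruitment section of the protocol article states: "A multifaceted approach to recruitment will be adopted, using two main strategies".

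- **Registry route.** Invitations go by post in weekly blocks of 100. "Blocks will be selected randomly, with minimisation used to ensure balance between factors that may affect outcomes"; these factors are sex, current age and age at diagnosis. Invitees may answer online or on paper.
- **Technology route.** "we will identify community-based organisations and support groups with an online presence for AYACCS in Sweden". "Organisations and support groups will be asked to place advertisements on their websites", and to use e-mail lists, newsletters and social networking sites as well. The advertisements link to the online survey and carry "a study log-in code unique to each organisation and technologically based recruitment type". The stated purpose of that code is "to allow for the examination of success of each technology-based recruitment strategy".
- **Target.** Sample size estimation gives one total, 365, not split by route. With a 40% response, "we estimate inviting 913 potential participants to achieve the required sample size".
- **Outcomes.** Aim 2 is attitudes to e-mental health. Table 1 lists receipt and type of support (formal, technology, informal) under the dependent variable. The section on actual help-seeking behaviour includes the option "e) social media support group", classes it as informal, and counts only support from a health professional as help-seeking.
- **Analysis.** Univariable models are followed by one multivariable logistic model with backward elimination at p<0.05, with exploratory subgroups by age and sex. Recruitment source is not a factor, covariate or stratum, and no sensitivity analysis by source is described.
- **Limitations.** The Discussion mentions the lack of compensation, the wide age range, survey length and the absence of a responder comparison for the mailed survey. It does not mention self-selection by recruitment route.

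**The concern.** The two routes reach people in different ways. One invites at random from a national register. The other relies on people who follow a cancer organisation or support group online and choose to click through. The second route bypasses the balancing on sex, age and age at diagnosis, and it is online from end to end.

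Two sets of results are exposed. The first is descriptive: attitudes to internet-delivered interventions and the type of support used. People found through online support communities plausibly differ on both, and a pooled mean or proportion then depends on how many volunteers happen to enrol. The second is the odds ratios for professional help-seeking. If the volunteers differ from registry respondents on both a predictor (stigma, social support, distress or sex, for example) and help-seeking, pooling without a source term can create or mask an association.

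**Working it through.** **1. The plan's own figure.** 365 / 0.40 = 912.5, rounded up to 913, as stated. The 365 itself cannot be reproduced, because no effect size or base rate is given. Under the stated response rate the mail-out alone would supply the sample, so the article does not say how many volunteers to expect. Their share *w* must be assumed; 10% to 50% is used below.

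**2. Descriptive results, proportions.** Pooled proportion = (1 − w) × p_registry + w × p_volunteer. Assume p_registry = 20% and N = 365.

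| Volunteer share | Volunteers at 1.5 times the rate (30%) | Volunteers at twice the rate (40%) | 95% CI half-width |
|---|---|---|---|
| 10% | 21% (+1 point) | 22% (+2) | 4.2 points |
| 25% | 22.5% (+2.5) | 25% (+5) | 4.3 to 4.4 |
| 50% | 25% (+5) | 30% (+10) | 4.4 to 4.7 |

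With registry rates from 15% to 30%, the shift runs from 0.8 to 15 points. It exceeds sampling error only when the share and the difference are both large.

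**3. Descriptive results, attitude scores.** If volunteers differ from registry respondents by *d* standard deviations, the pooled mean moves by w × d. The 95% half-width of a mean at N = 365 is about 1.96/√365 = 0.103 SD. The shift passes that when d > 0.103/w: about 1.03 SD at w = 10%, 0.41 SD at 25% and 0.21 SD at 50%. The documents give no value of d.

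**4. Odds ratios.** Assume a binary predictor with 50% prevalence, 20% help-seeking among those without it, and a volunteer entry rate that depends on the predictor, the outcome or both.

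| Volunteer entry | True OR | Pooled OR, w = 25% | Pooled OR, w = 50% | OR within volunteers |
|---|---|---|---|---|
| Doubled by the outcome only | 1.0 | 1.00 | 1.00 | 1.00 |
| Doubled by the outcome only | 2.0 | 2.00 | 2.00 | 2.00 |
| Doubled by each, multiplicatively | 1.0 | 1.10 | 1.13 | 1.00 |
| Doubled by each, multiplicatively | 2.0 | 2.19 | 2.25 | 2.00 |
| Doubled if either is present | 1.0 | 0.85 | 0.72 | 0.50 |
| Doubled if either is present | 2.0 | 1.71 | 1.44 | 1.00 |

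Selection on the outcome alone does no harm to the odds ratio. With multiplicative selection the odds ratio is right within each source, so a source term repairs it. In the either-present case the volunteers' own odds ratio is wrong (0.50 for a true 1.0). A source term cannot repair that; only the registry-only analysis avoids it.

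**5. A concrete mixture.** Assume 274 registry respondents (50% women, 20% help-seeking) and 91 volunteers (75% women, 40% help-seeking), with no sex effect in either.

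- Women: 27.4 + 27.3 = 54.7 of 205.25, or 26.65%.
- Men: 27.4 + 9.1 = 36.5 of 159.75, or 22.85%.
- OR = (54.7 × 123.25)/(150.55 × 36.5) = 1.23; log OR 0.205, SE 0.246, 95% CI about 0.76 to 1.99.

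The distortion is real but small against its own uncertainty at this sample size. Adjusting for source returns it to 1.00.

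**The case against.** Several stronger readings are tempting, and the documents do not bear them out.

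- **That the volunteer route samples directly on the regression outcome.** It does not. Social media support groups are classed as informal support, and the binary outcome counts professional support only. Any selection on that outcome is indirect. Selection on type of support and on online attitudes is more direct.
- **That any factor differing between the sources acquires a spurious association.** Selection must depend on both predictor and outcome, and the direction can go either way. Many factors likely to differ by source (sex, age, education, urban residence, distress, stigma, social support) are also in the full model, which limits residual distortion while they stay in it.
- **That the harm can be quantified.** The volunteer share and the differences by source are all assumed. The odds ratio of 1.23 above would usually be eliminated at p<0.05.
- **That the registry sample is unbiased.** It is random in invitation only; about 60% are expected not to respond. The article acknowledges limited representativeness and gives a reason for the second route, namely declining response to mailed surveys.

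It can also be said that pooling is inferred rather than stated, that the 913 figure suggests the target was planned on registry respondents, and that a full protocol or SAP may handle source. The first two are fair. On the third, the article already fixes the factor list, the strata and the elimination rule, all without source, and gives the log-in codes only a recruitment purpose. Followed as written, source plays no part in the analysis. That part of the concern stands.

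**Conclusion.** The concern holds in a limited form. Two differently selected groups enter one analysis, and the plan does not use the recorded source to separate or adjust for them. The clearest exposure is descriptive: attitudes to internet interventions and type of support. The exposure of the odds ratios is conditional on joint selection and runs in no fixed direction.

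The documents do not allow the bias to be sized. Under the stated assumptions it ranges from negligible (1 point, with 10% volunteers at 1.5 times a 20% rate) to about twice the sampling error (10 points against 4.7, with 50% volunteers at twice the rate). A true odds ratio of 1.0 moves to between 0.72 and 1.13 in the joint-selection scenarios.

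A reader might infer that the 365 must be counted on registry respondents alone. That is a trade-off, not a correction: it could need more mail-outs, and the article's assumptions do not require it.

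**What to change.** Add three statements to the statistical analysis section:

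1. Report attitudes to e-mental health and help-seeking (including type of support) separately for registry and technology-based respondents, alongside any pooled figure.
2. In the pooled univariable and multivariable logistic models, include recruitment source (registry versus technology-based) as a fixed covariate, exempt from backward elimination.
3. Repeat the models in registry respondents only as a sensitivity analysis. This is needed because a source covariate does not remove joint selection among the volunteers themselves.

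The cost is one extra model parameter and a little more analysis and reporting. Source can be derived from the log-in codes, and paper returns come only from the mail-out. The recruitment target stays as it is. Completion mode should not be forced into the models: paper is open only to mailed invitees, so mode is structurally tied to source, and choosing to answer online may itself reflect the attitudes that aim 2 measures.
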